**Propensity score model**

A logistic regression model was used to estimate the propensity scores for receiving treatment. The construction of the propensity score model involved selecting confounders from a large pool of candidates related to treatment selection. These candidates included baseline characteristics (37 variables), patient conditions from the pre-op form (12 variables), stone characteristics from the pre-op imaging form (13 variables), surgery-related characteristics from the surgery form (27 variables), and institutional and surgeon demographics (62 variables). The pool of candidate confounders was pre-screened based on the clinical importance scores provided by domain experts in the Data and Outcomes Committee (DOC), which included the study PI, site PIs, and statisticians. Variables were also assessed for their correlation with other variables. Within each category, variables were ranked based on their clinical importance and correlation scores. Correlation scores were defined by the number of correlated variables with a correlation coefficient greater than 0.3, considered moderate correlation (Cramér's V of 0.3). Variables that were less important or highly correlated with higher-ranked variables were removed. Specifically, we started from the top of the list and removed variables if they had a correlation coefficient exceeding 0.4 with higher-ranked variables, (a Cramér's V of 0.5 is considered strong correlation), while retaining the variable with higher clinical importance. This procedure, conducted without analyzing the outcome data, yielded a list of pre-screened confounders. The pre-screened confounders were further examined using univariate analysis to evaluate their associations with the surgical treatment across all enrolled participants in the study. Variables with a p-value less than 0.2 were selected and reviewed by the DOC. The final list of confounders was determined by the DOC, combining domain knowledge with the estimated strength of association. The list is shown in Table 1. We verified the performance of the propensity score model by comparing the distribution of confounders between treatment groups both before and after inverse probability weighting (IPW). Confounders with a standardized difference in median (SDM) greater than 0.25 after weighting were included in the outcome models for further adjustment.

**eTable 1.** Final List of Confounders Used in the Propensity Score Model

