| Domains                                   | Variables                                                                                                                                                                                                                                                                                                                                                                                                                                                                                                                      |
|-------------------------------------------|--------------------------------------------------------------------------------------------------------------------------------------------------------------------------------------------------------------------------------------------------------------------------------------------------------------------------------------------------------------------------------------------------------------------------------------------------------------------------------------------------------------------------------|
| Baseline Characteristics                  | experience with prior surgery, problems with blood cells, muscle problems                                                                                                                                                                                                                                                                                                                                                                                                                                                      |
| Pre-op variables                          | age, prior GU reconstruction, monogenic stone disease                                                                                                                                                                                                                                                                                                                                                                                                                                                                          |

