| Surgery variables                         | structural renal abnormality, primary clinical indication for surgery, surgery within 24 hours of symptom evaluation, restrictions to OR access                                                                                                                                                                                                                                                                                                                                                                                |
| Imaging variables                         | imaging type, number of stones, stone location, stone size                                                                                                                                                                                                                                                                                                                                                                                                                                                                     |
| Institutional and surgeon Characteristics | number of kidney stone patients evaluated in outpatient clinic during 2018-2019, the importance of patient age in surgeon's surgical decision-making, the importance of family's preference in surgeon's surgical decision-making, the importance of stone size in surgeon's surgical decision-making, the importance of availability of equipment in surgeon's surgical decision-making, surgeon's preference for URS versus PCNL for a 1.5 cm kidney stone, surgeon's preference for SWL versus PCNL for a 2 cm kidney stone |

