|                        | Structural CNS abnormality | 4
(4.3)           | 2
(4.3)                   | 26
(2.7)           | 9
(2.1)                    |
|                        | Developmental Delay        | 37
(39.8)         | 19
(41.3)                 | 113
(11.9)         | 58
(13.3)                  |
|                        | Epilepsy                   | 21
(22.6)         | 13
(28.3)                 | 65
(6.9)           | 32
(7.3)                   |
| Food insecurity, n (%) | Often True                 | 4
(4.3)           | 3
(6.5)                   | 9
(1.0)            | 3
(0.7)                    |
|                        | Sometimes True             | 4
(4.3)           | 0
(0)                     | 59
(6.2)           | 25
(5.7)                   |
|                        | Never True                 | 64
(68.8)         | 31
(67.4)                 | 761
(80.4)         | 358
(82.1)                 |
|                        | Missing/Unknown            | 21
(22.6)         | 12
(26.1)                 | 117
(12.4)         | 50
(11.5)                  |

**eTable 5.** Characteristics of Patients Who Underwent Shockwave Lithotripsy (SWL)

| Characteristics                                        |                       | SWL
(189)            |
|--------------------------------------------------------|-----------------------|-------------------------|
| Median age, median (IQR)                               |                       | 15.62
(12.53- 17.63) |
| Age Group, n (%)                                       | 08-11                 | 44
(23.3)            |
|                                                        | 12-15                 | 56
(29.6)            |
|                                                        | 16-18                 | 64
(33.9)            |
|                                                        | 19-21                 | 25
(13.2)            |
| Female sex, n (%)                                      | Female                | 100
(52.9)           |
| Race, n (%)                                            | White                 | 146
(77.2)           |
|                                                        | Black                 | 3
(1.6)              |
|                                                        | Asian                 | 1
(0.5)              |

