### 6.3 Control of Bias and Confounding

While all patients meeting eligibility criteria may be enrolled, we will restrict analysis to the first kidney stone surgery to avoid introducing clustering at the patient-level for the few (likely more complex) patients who would have multiple stone events over the 21-month enrollment period. Considering the large number of potential confounders, a pre-specified list of characteristics that includes but is not limited to the variables in Table 2 will be ascertained before surgery.

| Patient-level                         | Surgeon-level                                                                  |
|---------------------------------------|--------------------------------------------------------------------------------|
| Patient demographics                  | Years of out of residency                                                      |
| Body mass index                       | Experience with SWL, URS, and PCNL                                             |
| Pain at stone presentation            | Endourology fellowship                                                         |
| Insurance type                        | Pediatric urology fellowship                                                   |
| Number of stones                      | Preferences for URS, SWL, and PCNL                                             |
| Type of stone                         | Ownership in SWL collaborative                                                 |
| Single location vs. multicentric      | Ownership of surgery center                                                    |
| UTI at presentation or history of UTI | Surgeon gender                                                                 |
| Neurogenic bladder                    | Preferences for particular surgery                                             |
| Urinary tract anomaly                 | Importance of factors in surgery choice (radiation, reimbursement, discomfort) |
| Expectations about surgery            |                                                                                |
| Prior urinary tract reconstruction    | Hospital-level                                                          |
| Hydronephrosis                        | Hospital characteristics (e.g. bed number, nursing staffing)                   |
| Co-morbid conditions                  | Annual number of URS, SWL, PCNL performed at the hospital                      |

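### Sex, developmental delay, epilepsy and neurogenic bladder are missing from the propensity list without explanation, and the documents do not show that weighting balanced them

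*Combined protocol and SAP*

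**What the plan says.** Protocol 6.3 (Control of Bias and Confounding) promises that "a pre-specified list of characteristics that includes but is not limited to the variables in Table 2 will be ascertained before surgery". The table that follows lists, at patient level, demographics, neurogenic bladder and co-morbid conditions among others. The text after it commits to building the propensity models on these confounders.

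The SAP (Propensity score model) selects variables in steps. Candidates are ranked within category by clinical importance and correlation. The analysts then "removed variables if they had a correlation coefficient exceeding 0.4 with higher-ranked variables". The survivors are tested for association with treatment: "Variables with a p-value less than 0.2 were selected and reviewed by the DOC". The Data and Outcomes Committee (DOC) then sets the final list.

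The patient-level part of that list (eTable 1) reads:
- Baseline: "experience with prior surgery, problems with blood cells, muscle problems".
- Pre-op: "age, prior GU reconstruction, monogenic stone disease".
- Surgery: "structural renal abnormality, primary clinical indication for surgery, surgery within 24 hours of symptom evaluation, restrictions to OR access".
- Imaging: "imaging type, number of stones, stone location, stone size".

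Seven institution or surgeon items complete it, giving 3 + 3 + 4 + 4 + 7 = 21 variables. After weighting, confounders whose standardized difference (SDM) exceeds 0.25 are added to the outcome models.

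**The concern.** Four patient characteristics that fall under the protocol's own confounder table are absent from the model meant to remove treatment-selection bias. The SAP does not say at which step, or for what reason, each was dropped. They are not minor: developmental delay is more than three times as common in the PCNL arm as in the URS arm.

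Sex and neurological status could plausibly bear on symptom, anxiety and stress scores. Neurological status could also bear on imaging and stone clearance. The documents do not quantify these links. If the imbalances survive weighting, a difference in case mix could be read as a difference between procedures. The SAP's backstop, outcome-model adjustment when the SDM exceeds 0.25, is worded for confounders, which most naturally means the variables in eTable 1.

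The SAP's sensitivity analyses cover missing data, the imaging window and outcome misclassification. The analyses for unmeasured confounding promised in protocol 6.3 do not appear there.

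**Working it through.** **Inputs.** Counts come from eTable 4. Enrolled: PCNL 93, URS 946. Primary analytic cohort: PCNL 46, URS 436. Recomputed percentages match the printed ones, for example 37/93 = 39.8% and 113/946 = 11.9% for developmental delay.

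**Unweighted imbalance.** SMD = (p1 - p2) / sqrt{[p1(1 - p1) + p2(1 - p2)] / 2}, where p1 is PCNL and p2 is URS. For developmental delay, enrolled: (0.3978 - 0.1195) / 0.4152 = 0.67.

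| Variable | Enrolled, PCNL vs URS | SMD | Pearson p | Analytic, PCNL vs URS | SMD |
|---|---|---|---|---|---|
| Female | 43 vs 586 | -0.32 | 0.003 | 22 vs 266 | -0.27 |
| Developmental delay | 37 vs 113 | 0.67 | 3 × 10⁻¹³ | 19 vs 58 | 0.66 |
| Epilepsy | 21 vs 65 | 0.45 | 2 × 10⁻⁷ | 13 vs 32 | 0.57 |
| Neurogenic bladder | 17 vs 78 | 0.30 | 0.001 | 11 vs 39 | 0.41 |

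With the 189 shockwave lithotripsy patients as a third group, p is 0.0019, 1.2 × 10⁻¹², 6 × 10⁻⁹ and 0.00094. For comparison, hematologic disorder (9/93 vs 42/946) has an enrolled SMD of 0.21. It looks like the listed problems with blood cells, though that match is an assumption.

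**How much could a listed proxy remove?** Assume that muscle problems in eTable 1 is neuromuscular disorder in eTable 4 (33/93 vs 116/946, SMD 0.57). Its correlation φ with each omitted variable is not given, so φ is varied from 0 to the largest value the margins allow. A linear partial regression of the omitted variable on treatment, holding neuromuscular disorder fixed, gives the residual difference

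b = (r_k - r_m φ) / (1 - r_m²) × sqrt{p(1 - p) / [π(1 - π)]},

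where π = 93/1039, p is the pooled prevalence of the omitted variable, and r_k and r_m are the correlations of the omitted variable and of neuromuscular disorder with treatment. For developmental delay at φ = 0.4: (0.226 - 0.189 × 0.4) / (1 - 0.189²) × 1.231 = 0.192, and 0.192 / 0.4152 = 0.46.

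| Variable | φ = 0 | φ = 0.4 | Maximum φ |
|---|---|---|---|
| Developmental delay | 0.70 | 0.46 | 0.12 (φ = 1.00) |
| Epilepsy | 0.47 | 0.25 | 0.07 (φ = 0.73) |
| Neurogenic bladder | 0.31 | 0.07 | -0.15 (φ = 0.78) |

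At φ = 0.7, developmental delay is still at 0.29. For sex, the value at φ = 0 is about -0.33. Values at φ = 0 slightly exceed the crude SMDs because of the partial-regression denominator. This is an approximation for one proxy, not the study's weighting.

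**What cannot be computed.** Actual post-weighting balance needs patient-level data or eFigure 4, which is not reproduced in the text available here. eTable 4 counts patients, whereas clearance is analysed per kidney.

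**The case against.** Several points on the other side are sound.

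- **The p<0.2 step.** A reader might infer that leaving out variables with such small p-values breaks the SAP's own rule. It does not. The step applies only to variables that survive importance and correlation pruning, and the DOC then makes the choice. A variable can have p<0.2 and be left out properly.
- **Control after weighting.** A reader might also infer that weighting leaves the four variables uncontrolled. The documents do not show this. Muscle problems, prior genitourinary reconstruction, structural abnormality and primary indication may carry part of the neurological imbalance; at φ = 0.4 the first alone would take neurogenic bladder to 0.07. The 0.25 threshold applies after weighting, so unweighted SMDs do not fail it. The balance figure may already include these variables.
- **Patient-reported outcomes (PROs).** The PRO models adjust for baseline score, which should absorb part of any pre-operative difference. Patients unable to complete questionnaires may join for clearance and record surveillance only, so the developmental-delay imbalance need not carry into the PRO sample.
- **eTable 9.** Its different effects by sex (stress -11.19 in females, -1.01 in males) might be taken as evidence of confounding by sex. They show effect modification, and within-sex estimates are not confounded by sex. They give a reason to care about the sex mix if imbalance remains, but do not show that it remains.
- **Low ranking of sex.** In eTable 2, 36 + 47 = 83 of 126 urologists rated sex as of no or low importance to treatment choice, a possible reason for its removal. This does not extend to the comorbidities.
- **Surgeon items.** These did not displace patient items. Ranking was within category, and the protocol calls for both.

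What remains is the unexplained departure from protocol 6.3, the lack of an evident proxy for sex, developmental delay's need for a strong proxy, and an adjustment rule of unclear reach.

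**Conclusion.** The point holds as a gap in what the documents demonstrate. Four collected variables that fall under the protocol's confounder table are absent from eTable 1 without a stated reason. Their unweighted imbalance is 0.30 to 0.67 in absolute SMD among enrolled patients and 0.27 to 0.66 in the analytic cohort. Nothing available shows that weighting balanced them.

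The case is clearest for sex. It is next strongest for developmental delay, where a single proxy would need φ above 0.7 to bring the residual under 0.25. It is weaker for epilepsy and weakest for neurogenic bladder. These gradations rest on equating muscle problems with neuromuscular disorder, on an assumed φ and on a linear approximation. The size and direction of any effect on clearance or PRO estimates cannot be stated from the documents. Neither a breach of the SAP nor proven residual confounding is established.

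**What to change.** 1. State at which step, and why, each of the four variables left the list.
2. Report weighted standardized differences for all four and for the other patient-level variables in protocol 6.3 and eTable 4. Use differences in means or proportions, as protocol 6.3 describes. The SAP's difference in medians cannot serve for yes/no variables: developmental delay at 39.8% and 11.9% has median zero in both arms.
3. Say explicitly that the 0.25 outcome-model rule covers these variables, and apply it.
4. Re-run the weighted outcome models for stone clearance and PROs with sex, developmental delay, epilepsy and neurogenic bladder as covariates, at least as a sensitivity analysis whose covariate set is fixed before the re-run.

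Adding them to the outcome models is preferable to enlarging the propensity model. That model already has 21 variables for 93 enrolled PCNL patients (93/21 = 4.4 per variable) or 46 analysed (46/21 = 2.2), and more terms risk more extreme weights.

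The cost is SAP wording and a re-run on existing data. Intervals would be somewhat wider with 46 analysed PCNL patients, and the three neurological variables may be collinear. If they are, report the model with all four beside one with sex and developmental delay only.

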### Outcome model

Both the primary and secondary outcomes were compared using the IPW approach. The outcomes were compared using regression models with IPW and adjusted for unbalanced confounders after weighting. The analysis of PROs was conducted at 1-week, 3-weeks, 6-weeks, and 3-months after the index surgery adjusting for baseline scores.

### Analysis of heterogeneity of treatment (HTE)

HTE was analyzed by both stratified analyses and regression models with interaction terms. HTE of stone clearance was evaluated by stone size (<7mm, 7-10mm, 11-15mm, >15mm) and location (lower pole, non-lower pole, ureter). HTE of PROs was evaluated by patient age group (8-11, 12-15, 16-18, 19-21) and sex. Categories were defined *a priori* by the DOC.

### Missing data

We used multiple imputation (MI) to handle missing data. Variables used to impute missing data included all baseline covariates, treatment variable, and observed outcomes that were used in the analysis. Twenty imputed datasets were created and analyzed separately, and the results were combined using Rubin's rules to produce valid statistical inferences. MI was used for the analyses of stone clearance, PROs at week 1, and HTE of both primary and secondary analyses.

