**eAppendix 1. Statistical Analysis Plan**

The study aims to compare the effectiveness of Ureteroscopy (URS) and shockwave lithotripsy (SWL) as surgical treatments for kidney stone removal and patient experience in pediatric patients. The primary outcome is stone clearance, defined as the absence of any stone with a longest dimension greater than 4mm in an ultrasound (US) scan performed within 4-8 weeks post-surgery. If multiple images are available, the one closest to 6 weeks will be used. Secondary outcomes include patient experiences measured by patient-reported outcomes (PROs) using 5 PROMIS domains, DVSS, and QUIKSS at baseline (before surgery), and at 1 week (7 days +/- 3 days), 3 weeks (21 days +/- 7 days), 6 weeks (45 days +/- 7 days), and 3 months (90 days +/- 7 days) after surgery. We used propensity scores and inverse-probability-weighting adjustment to reduce treatment-selection bias when comparing outcomes.

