### Sensitivity analysis

We conducted a complete data analysis assuming the missingness was completely random. In addition, to assess the impact of potential missing not at random mechanisms on the study results for stone clearance, we performed a sensitivity analysis using pattern-mixture models. We assumed that patients with missing outcomes had different stone clearance rates compared to those without missing data. The scenarios included:

1. Patients with missing outcomes had a 100% stone clearance rate, regardless of the surgery received.
2. Patients with missing outcomes had a 0% stone clearance rate, regardless of the surgery received.
3. Patients with missing outcomes had stone clearance rates ranging from a -25% to 25% change from observed rates within each treatment group.
4. Patients with missing outcomes had stone clearance rates changing oppositely between the two treatments, ranging from 0% to 100%.

We also conducted a sensitivity analysis for the assessment window of the stone clearance outcome using ultrasounds obtained between 0 to 16 weeks, selecting those closest to the 6-week post-surgery time-point. Additionally, we performed a central review of 10% randomly selected post-op images. We calculated the sensitivity and specificity of the misclassification of the primary outcome and updated the weights after incorporating them with IPW to correct bias due to misclassification.

**eFigure 1.** The Pediatric KIDney Stone (PKIDS) Care Improvement Network

[figure not shown]

**eFigure 2.** Ultrasonographic Protocol Agreed Upon by PKIDS Investigators and Implemented as Standard Imaging Follow-Up After Surgical Intervention

EXAMINATION: [ ]

DATE: [ ]

COMPARISON: [ ]

TECHNIQUE: Grayscale sonographic image acquisition was performed of the kidneys and bladder.

FINDINGS:

BLADDER:

Stone visualized at UVJ: [No/Yes]

RIGHT KIDNEY:

Collecting system: [The calyces and pelvis are nondilated.]

Ureter: [The ureter is nondilated.]

Calculi: [No/Yes]

- If calculus present, measure the longest dimension of 3 largest stones

1. Location: [If present, PLEASE DESCRIBE for each measured stone: e.g., upper pole calyx; interpolar calyx; lower pole calyx; renal pelvis; ureteropelvic junction; proximal ureter; distal ureter]

- Size: [ ] mm

- Shadow: [No/Yes]

- Doppler: [Not applicable/Twinkle/No twinkle]

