Up to 60% of children with kidney or ureteral stones (hereafter referred to as kidney stones) require surgery. As for adults, surgery is indicated when a ureteral stone does not pass and for non-obstructing kidney stones that are too large to pass, cause infection, pain, or hematuria, and when patients choose treatment over surveillance. Surgical options include ureteroscopy (URS), shockwave lithotripsy (SWL), and percutaneous nephrolithotomy (PCNL), all of which use an energy source to break stones and require anesthesia. URS is an outpatient endoscopic surgery that accesses the ureters and kidneys per the urethra to fragment and remove the stones. SWL is a non-invasive outpatient procedure that targets stones in the kidney or ureter with x-ray or ultrasound and uses shockwaves generated outside the body to fragment them; the fragments pass down the ureter and the patient expels them in the urine. PCNL is a minimally invasive surgery in which a ~1cm flank incision is made, and a scope is passed through a tubular sheath into the kidney to fragment and remove the stone. There is typically a 1- to 2-night hospital stay. Many patients who undergo URS, SWL, or PCNL also have temporary tubes placed after the surgery to facilitate drainage, either internally (a stent) or externally (a nephrostomy tube). Proper treatment selection, which is directed by patient-specific factors and individual treatment goals, is the greatest determinant of successful outcomes.

Stone clearance is a surgical outcome that is important to patients because residual stone fragments lead to painful stone passage, ED visits, and surgical retreatment. The comparative effectiveness of URS, SWL, and PCNL with respect to stone clearance for pediatric patients is unclear because of five characteristics of prior studies.

- Biased measurement of stone clearance due to use of multiple imaging modalities with different sensitivities.
- Combining patients who had repeated treatments with those who had one treatment in a single group.
- Heterogeneity of the size of residual stone fragments after surgery considered “clinically insignificant”.
- No consideration of factors impacting treatment choice and outcomes (*e.g.*, surgeon characteristics).

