#### **4.5 EHR Surveillance**

Patient participant data from ED visits, hospitalizations, clinic visits, and surgical (re)treatment will be obtained during the duration of clinical follow-up in PKIDS. A member of the research team at each site will manually access the data at the PKIDS site and enter it into the secure electronic database (e.g. OnCore). For the 8 PEDSnet sites, outcomes will also be ascertained by querying the PEDSnet Common Data Model at each PEDSnet site. Patient participants may be contacted to verify information obtained about healthcare encounters that occurred within 3 months of the index surgical procedure.

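### As written, the imputation model for 4-8 week stone clearance leaves out out-of-window ultrasounds, retreatment and unplanned encounters, all of which the study collects

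*Combined protocol and SAP*

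**What the plan says.** The SAP takes the primary outcome from an ultrasound "performed within 4-8 weeks post-surgery. If multiple images are available, the one closest to 6 weeks will be used". Its Missing data section gives the imputation variables: "Variables used to impute missing data included all baseline covariates, treatment variable, and observed outcomes that were used in the analysis". It adds that "Twenty imputed datasets were created and analyzed separately", combined by Rubin's rules, and that "MI was used for the analyses of stone clearance, PROs at week 1, and HTE of both primary and secondary analyses". The phrase about observed outcomes is not defined.

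Scans outside 4-8 weeks appear only under Sensitivity analysis, in a separate analysis "using ultrasounds obtained between 0 to 16 weeks, selecting those closest to the 6-week post-surgery time-point", reported in eTable 11. The same section lists pattern-mixture scenarios that shift clearance among the missing as a group, for example: "Patients with missing outcomes had stone clearance rates ranging from a -25% to 25% change from observed rates within each treatment group".

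The protocol collects further post-surgery information. Section 4.5 says: "Patient participant data from ED visits, hospitalizations, clinic visits, and surgical (re)treatment will be obtained during the duration of clinical follow-up in PKIDS". The abstract sets assessment of retreatment and unplanned encounters at 3 months. Section 1.2 explains their relevance: "residual stone fragments lead to painful stone passage, ED visits, and surgical retreatment". The SAP names none of these as imputation variables.

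**The concern.** Imputation is valid when, given the variables in the model, being unscanned carries no further information about clearance. A child's chance of a scan at 4-8 weeks plausibly depends on what happened after surgery: symptoms, an earlier scan, an ED visit or a second operation. Each also bears on whether stone remains. If the model holds none of this, it assumes more than the collected data require.

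The share of data affected is large. Section 6.4 assumes 15% loss to follow-up, yet more than half of enrolled PCNL and URS patients are outside the primary analytic cohort. A scan at week 3 or week 10 is direct, if imperfect, evidence about a kidney whose 4-8 week status is unknown. On the stated list it does not inform that kidney's imputed value. Both the overall PCNL-URS contrast and the large-stone contrast depend on these imputations.

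**Working it through.** **1. Share without the outcome (eTable 4).** PCNL: 93 - 46 = 47, and 47/93 = 50.5%. URS: 946 - 436 = 510, and 510/946 = 53.9%. Together 557/1039 = 53.6%. This assumes patients are outside the cohort because no usable 4-8 week scan exists. eTable 4 counts patients, whereas clearance is analysed by kidney.

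**2. Published contrasts, reproduced by subtraction.** eTable 13: 66.7 - 73.1 = -6.4. eTable 11: 72.4 - 72.1 = 0.3. For stones over 15 mm: 81.1 - 60.3 = 20.8 (stated 20.7) and 92.5 - 57.1 = 35.4 (stated 35.3). All agree within rounding.

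| | eTable 12: misclassification-corrected | eTable 11: 0-16 week scans | eTable 13: MI, 4-8 weeks |
|---|---|---|---|
| PCNL, overall | 63.9 | 72.4 | 66.7 |
| URS, overall | 70.5 | 72.1 | 73.1 |
| PCNL-URS, overall | -6.5 (-29.1 to 16.1) | 0.3 (-17.2 to 17.8) | -6.4 (-22.8 to 10) |
| PCNL, >15 mm | 93.1 | 92.5 | 81.1 |
| URS, >15 mm | 51.4 | 57.1 | 60.3 |
| PCNL-URS, >15 mm | 41.7 (16.3 to 67.1) | 35.3 (15.5 to 55.1) | 20.7 (-15.4 to 56.8) |

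**3. Gap between eTable 11 and eTable 13.** Overall: 0.3 - (-6.4) = 6.7 points, of which PCNL contributes 72.4 - 66.7 = 5.7 and URS 73.1 - 72.1 = 1.0. Over 15 mm: 35.3 - 20.7 = 14.6 points, of which PCNL contributes 92.5 - 81.1 = 11.4 and URS 60.3 - 57.1 = 3.2. Over 15 mm, the two scan-based tables agree closely for PCNL (93.1 and 92.5) and both intervals for the difference exclude zero. The MI interval does not.

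**4. How many URS kidneys have only an out-of-window scan.** Take SE = (interval width)/3.92 and implied n = p(1-p)/SE².
- eTable 11: width 75.4 - 68.9 = 6.5, SE = 1.66 points, n = 0.721 × 0.279/0.01658² = about 732.
- eTable 12: width 74.7 - 66.2 = 8.5, SE = 2.17 points, n = 0.705 × 0.295/0.02168² = about 442, close to the 436 URS patients in the cohort.
- Difference: 732 - 442 = about 290. Rounding of the limits alone gives 257 (710 - 453) to 323 (755 - 432).

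eTable 6 gives 485 + 479 + 98 + 8 = 1,070 URS kidneys, so 290 is about 46% of the 1,070 - 442 = 628 without an in-window scan. The calculation ignores weighting and assumes eTable 12 uses the 4-8 week window.

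**5. What a wrong assumption would cost.** Bias in an arm's rate = (share missing) × (difference between true clearance in the missing and what the model predicts). For an assumed 10-point difference: 0.505 × 10 = 5.1 points in PCNL and 0.539 × 10 = 5.4 in URS. For 20 points: 10.1 and 10.8. The documents do not give the true difference. Equal bias in both arms would largely cancel in the contrast; unequal bias would not.

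**The case against.** The strongest reply is that the SAP sentence is not exhaustive. It says the variables included certain items, and the undefined reference to observed outcomes could cover the PROs or even 0-16 week clearance. A reader might infer that imputation rests on baseline data alone and that the other scans are ignored. The text does not establish that. What stands is that the stated list names none of these variables, and that the list needs defining.

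Second, the scans are not discarded. eTable 11 analyses them overall, by size and by location, and the pattern-mixture scenarios bracket outcome-dependent missingness at group level. This is fair, but neither uses an individual child's post-surgery information to estimate 4-8 week clearance in all treated kidneys. The 0-16 week analysis changes the window and, as described, leaves out kidneys never scanned. The scenarios shift whole groups by assumption.

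Third, the tables cannot assign the shift to the imputation model. eTable 11 differs from eTable 13 in window as well as method, the overall intervals overlap heavily, and the corrected eTable 12 contrast (-6.5) is almost the same as MI (-6.4). Overall URS rates differ by only 1.0 point between eTables 11 and 13. All of this stands.

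Fourth, the remedy may be hard to estimate. Protocol section 4.3.2 plans one routine ultrasound at 6 weeks ± 2, so the number of kidneys scanned both inside and outside the window is unknown. A separate PCNL model on 46 observed patients might barely be estimable. This also stands and shapes the fix.

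**Conclusion.** The point holds as a weakness in the stated method, and it should be corrected. With 53.6% of patients outside the primary analytic cohort, the listed model leaves out collected information that plausibly predicts both clearance and being scanned. Results are sensitive to how these kidneys are handled: 14.6 points for stones over 15 mm, where the interval excludes zero with 0-16 week scans but not with MI, and 6.7 points overall, well inside either interval. The conclusion assumes that the list means what it says, and the figure of 290 kidneys is approximate.

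Three stronger readings are not supported:
- **That MI overwrites observed evidence of residual stone.** No in-window result is replaced. In the PCNL arm, the rate with 0-16 week scans is higher than with MI, not lower.
- **That the size of a PCNL bias can be recovered.** Backing out a rate for PCNL kidneys scanned only outside the window rests on about 25.8 - 18.1 = 7.7 effective kidneys (eTables 11 and 12). Their ratio is 1.43; at 1.3 the result is impossible: (72.4 × 1.3 - 63.9)/0.3 = 100.7%.
- **That the shift can be judged against a planned PCNL-URS effect.** Section 6.4 states power for URS-SWL and PCNL-SWL clearance only.

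The role of MI is itself unclear. The SAP makes the complete-data analysis a sensitivity analysis, yet eTable 4 labels the scanned patients the primary analytic cohort and eTable 13 reports MI separately.

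**What to change.** Keep 4-8 week clearance as the outcome and leave the propensity and outcome models unchanged. In the SAP's Missing data section:

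1. List every imputation variable and define the observed outcomes referred to.
2. If they were not used, add as imputation-only auxiliaries: (a) retreatment of that kidney, and ED visits or hospitalizations to 3 months; (b) clearance status and week of the nearest out-of-window ultrasound, with an indicator for no such scan.
3. Fit the auxiliary relation pooled across arms with treatment in the model, penalised if sparse, and not separately within PCNL.
4. Report how many kidneys, by arm, have both an in-window and an out-of-window scan.
5. Report overall and stone-size MI results from this model beside the existing MI.

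The cost is SAP wording and a rerun on data already collected. The downside is a larger imputation model whose link between out-of-window and in-window status rests on the kidneys with both scans. If these prove few, the retreatment and encounter auxiliaries can still be added, and the limitation should be stated.
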